#### Primary outcome measures cluster RCT

The first primary outcome measure is *social participation *measured with the Birchwood Social Functioning Scale (SFS) [44]. It measures social functioning on seven domains: social engagement/withdrawal, interpersonal behavior, pro-social activities, recreation, independence-competence, independence-performance, and employment/occupation. The SFS is a reliable, valid, sensitive to change, instrument with a high internal consistency (α = 0.80) [44].

The second primary outcome measure is victimization related to societal participation and includes the following:2.*Criminal victimization* will be measured with the Dutch version of the Safety Monitor, developed by the Dutch Ministry of Security and Justice [45], and strongly resembles the International Crime Victimization Survey [46]. It is a self-report questionnaire in which section 4 measures victimization on 15 crimes: burglary, theft from car, car theft, theft of other motorized vehicles, bicycle theft, (attempt to) robbery, theft (other than previously categorized), sexual intimidation or assault, threats (of violence), physical assault, vandalism, identity fraud, fraud with buying/selling items/services, hacking, cyber bullying. For each incident reported in the past 12 months, participants are asked to give more information about the incident.3.*Perceived safety* will also be measured with the Safety Monitor. The participant is asked whether they ever feel unsafe (yes/no) and how often (often/sometimes/rarely).4.*Discrimination and stigmatization* is assessed by the Discrimination and Stigmatization Scale (DISC-12) [47]. This scale consists of four subscales: unfair treatment, stopping self, overcoming stigma, positive treatment. The DISC-12 contains 32 items answered on a 4-point scale ranging from ‘no difference (0)’ to ‘a lot (3)’. A ‘not applicable’ answer is available when the participant was not involved in the described situation. Psychometric properties are considered good, Cronbach’s alpha is 0.78 and the inter-rater reliability ranges from 0.62 to 0.95.

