### RCT analyses

#### Sample size

Sample size is calculated using the model of Twisk [56]. This model is suitable for multiple measurements over time, but can also be used for cluster randomization. With the ratio of the number of subjects in the compared groups being 1 (*r*), a correlation coefficient of the repeated measurements of 0.20 (ρ), a conservative difference between the groups in the mean value of social functioning of 0.25 (*v*), and a power of 1-β = 0.80, the number of participants needed is 151 for each condition at T2 measurement (α = 0.05, two-tailed). Taking into account an attrition rate of 15% for loss due to follow-up or consent withdrawal, 173 participants per condition need to be recruited to achieve the required power.$$ N=\frac{Z\left(1-\alpha /2\right)+Z\left(1-\beta \right)\ 2\ \sigma 2\left(r+1\right)\left[1+\left(T-1\right)\rho \right]}{v2r\ T} $$

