#### Statistical analyses

Data will be analyzed according to the ‘intention to treat’ principle, meaning that F-ACT teams (and thus clients) that are assigned to either experimental or control condition in randomization, will be analyzed accordingly. Because of the cluster design and multiple measurements over time, generalized linear mixed models (GLMM) will be used with SPSS (version 22); depending on the distribution of the outcome variable a logistic regression model or a linear regression model will be adopted. GLMM is robust with respect to missing data [57], which is not uncommon in research among outpatients with SMI. Therefore, multiple imputation is not necessary. To analyze the effect of the Victoria intervention on the main outcomes, differences in societal participation and victimization, both conditions will be compared after 9 and 18 months follow-up with time as a categorical variable. Measurements over time are nested within participants; therefore, random slopes will be added for time. Random intercepts will be added for the participants. The same procedure will be adopted for secondary outcome measures. Furthermore, possible confounders will be examined, such as socio-demographic characteristics, current diagnosis, number of years in MHC, or perpetration on whether they need to be added to the model. Only significant confounders will be added to the final model. In all analyses performed, two-tailed *p*-values < 0.05 are considered significant. Finally, Akaike’s Information Criterion (AIC) will be used for the selection of the final model that fits the data best and is the most generalizable [58].

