## Discussion

Outpatients with SMI experience high rates of victimization, discrimination and stigmatization [11–17]. These adversities are important barriers to rehabilitation and societal participation [21]. This study is the first to evaluate an intervention aiming at recognition of victimization and other adversities, that also targets outpatients’ insight and coping skills with regard to possible risks to ensure safe societal participation. The aim of this first trial on the Victoria intervention is to gain insight into the implementation process and effectiveness of the Victoria intervention in reducing victimization (among other adversities) and increasing societal participation, on both the team level and the client level.

A major strength of this study will be the large sample size of outpatients with SMI, leading to sufficient power, which is often a problem in similar trials [59]. Only clients that are unable to fill out the questionnaire during the inclusion period of 6 months, due to insufficient understanding of the Dutch language, prolonged clinical admission, or severe symptomatology, will be excluded from the study. This, as well as the participation of multiple mental health centers, enhances generalizability of results.

This is, to our knowledge, the first study to address victimization and other adversities as a barrier for societal participation. In relation to this, we incorporated a broad range of outcome measures. Many previous studies on victimization only take into account clinical outcome measures or socio-demographic variables such as living situation [13, 14]. Although some studies include the influence of victimization on, for example, quality of life, this study includes a broad range of social outcome measures, such as social functioning and social support. These outcome measures are likely to be influenced by victimization or other adversities in the social domain [60, 61].

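### The 151 per arm gives 80% power only for an unadjusted average of the two follow-ups with correlation 0.20 or lower; fixing the T0 score as a covariate would make it less fragile at no extra recruitment

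*Protocol article*

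**What the plan says.** The sample size section of the protocol article uses a repeated-measures formula. Its inputs are an allocation ratio of 1, "a correlation coefficient of the repeated measurements of 0.20", "a conservative difference between the groups in the mean value of social functioning of 0.25" and "a power of 1-β = 0.80". The result is 151 "for each condition at T2 measurement (α = 0.05, two-tailed"). The section gives no value for the number of measurements T or for the standard deviation, and no source for the correlation.

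The statistical analyses section plans a mixed model in which "both conditions will be compared after 9 and 18 months follow-up with time as a categorical variable". Covariates are drawn from an open list of possible confounders (socio-demographics, diagnosis, years in care, perpetration) and are kept only if significant. The T0 value of the outcome is not named in that list, and its role in the model is not stated. Table 1 shows the SFS collected at T0, T1 and T2. The Discussion presents the sample size as a major strength, "leading to sufficient power".

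**The concern.** A sample size based on an average of repeated scores depends on how strongly those scores correlate. The stronger the correlation, the less the second score adds and the more clients are needed. A low value such as 0.20 is therefore the favourable direction in this formula, and nothing in the article supports it. The 80% claim also belongs to one particular contrast, the unadjusted average of two follow-ups, which the analysis section does not name as the primary comparison.

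The T0 score is the natural protection. If the correlation is higher than assumed, an unadjusted average loses power, whereas a baseline-adjusted one generally recovers it because T0 then predicts the follow-ups better. A rule that keeps covariates only when significant does not guarantee that adjustment. At stake is avoidable loss of precision on the first primary outcome, and a power statement that holds more narrowly than the Discussion suggests.

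**Working it through.** **Inputs.** From the sample size section: difference v = 0.25, correlation ρ = 0.20, ratio r = 1, two-sided α = 0.05, power 0.80. Assumed: σ = 1, so that v is a standardised difference. T is not stated and is inferred below. (1.960 + 0.842)² = 7.849.

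**Reproducing 151.** Reading the printed formula with its squares:

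n per arm = 7.849 × 2 × f / 0.0625, with f = [1 + (T − 1)ρ] / T.

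- T = 1: f = 1, n = 252
- T = 2: f = 0.60, n = 150.7, so 151
- T = 3: f = 0.467, n = 118

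Only T = 2 gives the stated figure (power at 151 is 80.1%). A one-sided test with T = 2 would give 119.

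**Sensitivity to ρ, and the effect of adjusting for T0.** Without adjustment, f = (1 + ρ)/2. With T0 as covariate and one common correlation across all three waves, the covariance of T0 with the follow-up mean is ρ, so f = (1 + ρ)/2 − ρ². Power at 151 is Φ(0.25/√(2f/151) − 1.96). The document gives no ρ other than 0.20, so the remaining rows are assumptions. All figures are before clustering.

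| ρ | Unadjusted: n per arm | Unadjusted: power at 151 | T0-adjusted: n per arm | T0-adjusted: power at 151 |
|---|---|---|---|---|
| 0.20 | 151 | 80.1% | 141 | 82.7% |
| 0.25 | 157 | 78.5% | 142 | 82.5% |
| 0.30 | 164 | 76.9% | 141 | 82.7% |
| 0.40 | 176 | 73.8% | 136 | 84.0% |
| 0.50 | 189 | 70.8% | 126 | 86.7% |
| 0.60 | 201 | 68.0% | 111 | 90.6% |
| 0.70 | 214 | 65.4% | 91 | 95.2% |

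The adjusted factor peaks at ρ = 0.25, where f = 0.625 − 0.0625 = 0.5625 and n = 141.3, so 142. Under these conditions power at 151 does not fall below 82.5%.

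**Where that floor weakens.**

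- Correlation decaying with time (AR(1)) at 0.4: f = 0.70 − [(0.4 + 0.16)/2]² = 0.70 − 0.0784 = 0.6216, power 78.7%.
- Follow-up/follow-up 0.7 and baseline/follow-up 0.4: f = 0.85 − 0.16 = 0.69, n = 174, power 74.4%.
- T2 alone with T0 adjusted: f = 1 − ρ². At ρ = 0.20, f = 0.96, n = 242, power 60.1%. At ρ = 0.50, power is 70.8%. T2 alone without adjustment needs 252, with power 58.4%.

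**Clustering.** No intracluster correlation (ICC) is among the stated inputs. Eight teams give 151/4 ≈ 37.75 analysed clients per team. With an assumed ICC of 0.01 or 0.02, the design effect is 1 + 36.75 × ICC = 1.37 or 1.73 (rounded). Power of the adjusted average at ρ = 0.25 then falls to 69.7% or 59.4% by normal approximation, and to 54.6% or 45.5% with 6 degrees of freedom for eight teams.

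**The case against.** The strongest reply is that the article does not say T0 is left out. Its list of confounders is open, T0 could enter as a level of categorical time, and a condensed article may leave this to an analysis plan that is not shown. That stands: a reader might infer that baseline is ignored, and the text does not support it. What remains is that the covariate rule the article does state, retention by significance, would not secure the adjustment.

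A reader might also infer that 0.20 is wrong, because the SFS is described as an "instrument with a high internal consistency" (α = 0.80). Dividing 0.20 by 0.80 gives a true-score correlation of 0.25, which looks low. But internal consistency is not stability over 9 months, and the same sentence calls the scale sensitive to change. The documents do not show what the correlation is.

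A third tempting reading is a change-from-baseline analysis, which at ρ = 0.20 would need about 302 per arm and have 51% power at 151. No section states that contrast, so the figure is hypothetical.

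Finally, it may be said that baseline adjustment does not make the power independent of ρ. That is correct. The planned random slopes for time do not imply equal correlations, and comparisons at each follow-up separately fall outside the floor.

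**Conclusion.** The point holds in a limited form. The 151 is the size for an unadjusted average of two follow-ups with σ = 1 and ρ = 0.20. Before clustering, power reaches 80% there only if ρ is 0.20 or lower, falling to 65% at an assumed 0.70. Fixing T0 as a covariate improves on this at every common ρ shown, with at least 82.5% power at 151, provided the correlations are roughly equal across waves and the contrast is the average of the two follow-up differences.

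Two further conclusions would go too far. The trial's power should not be restated as 65–80%, because the range of ρ is assumed. Nor does the adjustment make 151 sufficient, because the eight teams are not yet in the calculation. The arithmetic concerns the SFS. For the other primary outcomes the case for using T0 is the same in principle, but no power figure is derived here.

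**What to change.** In the statistical analyses section, specify for the SFS:

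- T1 and T2 as outcomes;
- the client's T0 SFS score as a fixed covariate outside the significance rule, or equivalently a common baseline mean in both arms;
- the average of the 9- and 18-month differences as the primary contrast, since that is what 151 was sized for.

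Use the T0 value in the same way for the other primary outcomes.

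In the sample size section, state T = 2 and σ = 1, and give the source of 0.20 or say that it is an assumption. Show power over ρ = 0.2–0.7 with factor (1 + ρ)/2 − ρ², plus at least one case with unequal correlations, as a sensitivity range. Then apply the inflation for team clustering before making any statement about sufficient power.

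The cost is wording and one recalculation. T0 is already collected, so the adjustment itself needs no more clients; whether clustering does is a separate question that the recalculation must answer.

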## Background

In most western countries, deinstitutionalization has led to an increase of community-based care with a focus on promoting the recovery and societal integration of people with severe mental illness (SMI) [1]. To achieve successful integration into community life, psychiatric rehabilitation methods were developed in order to support people with SMI to regain a meaningful life and valued social roles [2, 3]. Within the field of psychiatric rehabilitation, several evidence-based practices can be identified. The Boston Approach to Psychiatric Rehabilitation (BPR) has proven to be effective in promoting new perspectives, role functioning, and life satisfaction [4, 5]. Another evidence-based rehabilitation intervention is the Individual Placement and Support (IPS) model of supported employment [6]. Employment specialists successfully support clients to search for and get a job, and also coach clients about working situations in order to maintain employment.

There are still substantial challenges to work on in community-based care, especially concerning supporting clients in their social and community participation. A lack of support in these areas may lead to unemployment, poverty, social isolation and even imprisonment [7]. Studies have also shown that these negative consequences may lead to an increase of victimization rates [8–10]. Not only are people with SMI more likely to experience victimization than other community members, in contrast to popular public belief, they are also more likely to become a victim of a crime rather than being the perpetrator [11–15]. Prevalence rates of violent victimization among persons with SMI range between 7 and 56% in the previous year – 11 times greater than the general population [8]. A recent nationwide study in the Netherlands examined prevalence rates of several types of victimization and found that almost 20% of people with SMI were a victim of serious crimes in the previous year, such as sexual harassment/assault, violence, and physical assault [11]. In most cases, the victim knew the perpetrators of these crimes.

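### The 151 per condition is derived for mean social functioning only, yet sufficient power is claimed without limit although criminal victimization and perceived safety are also primary outcomes

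*Protocol article*

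**What the plan says.** The primary effectiveness question (Objective and research questions) asks about societal participation and victimization together. Table 1 and the section on primary outcome measures list four primary measures: the SFS, criminal victimization, perceived safety and the DISC-12.

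The Sample size section has one calculation. It rests on "a conservative difference between the groups in the mean value of social functioning of 0.25", "a correlation coefficient of the repeated measurements of 0.20", "and a power of 1-β = 0.80" and "α = 0.05, two-tailed", and arrives at 151 per condition at T2.

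Perceived safety has two parts: "The participant is asked whether they ever feel unsafe (yes/no) and how often (often/sometimes/rarely"). Criminal victimization covers 15 crimes over the past 12 months, with details for each incident. How it is summarised is not fixed.

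For the models, Statistical analyses says that "depending on the distribution of the outcome variable a logistic regression model or a linear regression model will be adopted".

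The Discussion, directly after restating the aim of reducing victimization, says: "A major strength of this study will be the large sample size of outpatients with SMI, leading to sufficient power".

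**The concern.** A calculation for a difference in means says nothing by itself about a yes/no outcome, an ordinal grade or a count of incidents. The power claim in the Discussion is not limited to the outcome for which it was derived. If the trial finds no difference in criminal victimization or in feeling unsafe, a reader could take that as a negative result from an adequately powered trial, although the article gives no figure to support this.

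The named models add a smaller problem. Perceived safety is collected as what amounts to four ordered levels, and criminal victimization can be counted. A yes/no logistic model would drop the grade or the count, and a linear model suits a count with many zeros poorly.

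**Working it through.** **Reproducing the 151.** Inputs from Sample size: two-sided alpha 0.05, power 0.80, v = 0.25, ρ = 0.20, r = 1. Neither σ nor T is given a value there. I take σ = 1 (standardised) and read the flattened exponents as squares:

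N = (1.960 + 0.8416)² × σ² × (r + 1) × [1 + (T − 1)ρ] / (v² × r × T)

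- T = 1: 7.849 × 2 × 1.0 / 0.0625 = 251.2
- T = 2: 7.849 × 2 × 1.2 / 0.125 = 150.7, rounded up to 151
- T = 3: 7.849 × 2 × 1.4 / 0.1875 = 117.2

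So 151 is a two-follow-up figure for a 0.25 SD difference in a mean.

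**Carrying it over to a yes/no outcome.** I give the binary outcomes the same repeated-measures gain, which assumes that ρ = 0.20 applies to them too. The effective number per condition is 151 × 2 / 1.2 = 251.7 with both follow-ups averaged, or 151 at one follow-up. Team clustering is ignored.

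Power = Φ( |p₁ − p₂| / √{[p₁(1 − p₁) + p₂(1 − p₂)] / n} − 1.960 )

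The rate detectable with 80% power needs no effect-size conversion. It is the p₂ at which the ratio equals 1.960 + 0.8416 = 2.802. For p₁ = 0.20 and n = 251.7, p₂ = 0.110: 0.0897 / √(0.2581 / 251.7) = 2.80.

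For an assumed effect, the usual logit conversion of 0.25 SD gives an odds ratio of exp(0.25 × π/√3) = 1.57. At a 20% control rate this is 20% vs 13.7%: 0.0629 / √(0.2783 / 251.7) = 1.89, and Φ(1.89 − 1.96) = 0.47.

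| Control rate | 80% power, both follow-ups | 80% power, one follow-up | Power at OR 1.57, both | Power at OR 1.57, one |
|---|---|---|---|---|
| 20% | fall to 11% | fall to 9% | 47% | 31% |
| 30% | fall to 19% | fall to 17% | 60% | 40% |
| 40% | fall to 28% | fall to 25% | 68% | 47% |
| 50% | fall to 38% | fall to 34% | 72% | 50% |

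A pooled-variance test moves the detectable rates by less than 0.2 percentage points (the 17% becomes 16.4%) and power by half a point or less.

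The control rates are assumptions. The only nearby figures are in the Background: "almost 20% of people with SMI were a victim of serious crimes in the previous year", and a range of 7–56% for violent victimization. The outcome here covers 15 crimes, including thefts and fraud, so its rate may well exceed 20%. At 7%, power for OR 1.57 is 22% with both follow-ups and 15% with one.

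**Other conversions.** With Cohen's h = 0.25 the effect is 20% vs 11.0% or 50% vs 37.6%, and power is about 80% with both follow-ups and 58% with one. With 0.25 of the control-arm binomial SD, 20% becomes 10%, and power is about 88% and 68%.

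**A comparison for scale scores.** A 0.25 SD difference in a mean has 80% power with both follow-ups and 58% with one. The loss from using one follow-up is therefore not peculiar to the binary outcomes.

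**The case against.** The strongest reply is that the Sample size section openly names social functioning, which is listed as the first primary outcome, and that sizing a trial on one named primary is common. That is fair for the 151 itself. It does not cover the Discussion, where the claim names no outcome and follows a restatement of the victimization aim.

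A reader might infer that power for victimization is simply 45–70%. The document does not support that as a flat figure. A standardised mean difference has no unique binary equivalent, and Cohen's h puts power at about 80% with both follow-ups. Near a 20% rate, though, that conversion reaches 80% because it implies a fall to 11%, a larger effect than OR 1.57.

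A reader might also infer that only a halving can be detected. With both follow-ups the detectable relative fall is 45% at a 20% rate, but 36% at 30%, 29% at 40% and 25% at 50%.

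Nor is everything under victimization affected alike. The DISC-12 can take the linear model, where a standardised 0.25 with the same correlation has the stated power before clustering.

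Finally, the article does not say that criminal victimization will be made yes/no or that frequency grades will be discarded, and a cumulative-logit model is itself a form of logistic regression. Outcome-by-outcome scoring may be left to the full plan. What stands is narrower: the article names two model types, and neither, in its ordinary form, suits a four-level grade or a zero-heavy count.

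**Conclusion.** The point holds in limited form. The 151 is supported for a 0.25 SD difference in mean social functioning and for nothing else that the article shows. For criminal victimization and perceived safety, power is not stated, so the unrestricted claim in the Discussion is unsupported.

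If these two are analysed as yes/no, the detectable falls in the table are the firmest guide to size, because they need no effect-size conversion. They rest on 151 analysed per condition, ρ = 0.20 and control rates of 20–50%. The 47–72% (both follow-ups) and 31–50% (one) also require an odds ratio of 1.57.

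All of these are best-case figures. They leave out team clustering. The both-follow-ups figures also average 9 and 18 months, whereas the plan compares conditions at each with time categorical. For criminal victimization, a 12-month recall at 9 months reaches about three months before baseline and overlaps the window at 18 months, which would dilute the earlier contrast.

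**What to change.** 1. In Sample size and in the Discussion, limit the 80% and sufficient-power statements to social functioning. For criminal victimization and perceived safety as yes/no outcomes, give the detectable differences over a range of control rates, for both follow-ups and for one, labelled as best-case figures before clustering. Say that a null result on these outcomes does not show absence of effect. Any power figure for an assumed odds ratio should carry its assumptions.
2. In Statistical analyses, add a cumulative-logit mixed model for perceived safety as one four-level outcome (never, rarely, sometimes, often). If criminal victimization is summarised as a count, use a negative binomial mixed model with log link instead of a linear one. Keep the yes/no versions as supportive.

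No extra data or participants are needed. The costs are a less favourable power statement and effect measures (cumulative odds ratios, rate ratios) that are slightly harder to explain. The power gain from the ordinal model is modest: 76% or 79% against 72% for yes/no, under two assumed splits of the four levels, OR 1.57 and both follow-ups. No gain has been calculated for the count model; the case for it is fit.

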A final strength of the study is the multi-method approach. A process evaluation will be conducted to examine the implementation process of the intervention. Studies with a similar target population that examine complex interventions in a RCT often find no treatment effect, due to, for example, implementation or fidelity issues [62]. Within the design of an RCT, normally, there is little room for examining the implementation process, leading to a black box in explaining the results. Therefore, the UK Medical Research Council advises conducting a process evaluation, to understand context mechanisms and provide insights on implementation and fidelity [63]. For this reason, we do include a process evaluation and a longitudinal follow-up on effects, using a cluster RCT.

One of the main challenges in this study lies in the fact that the Victoria intervention is a complex intervention, encompassing characteristics of the local context, and the complexity of causal relations between intervention and outcomes [36]. MHPs in the participating teams sometimes work in multiple teams or, due to reorganization, they shift from one team to the other. This brings challenges in the implementation of the intervention. To address this, a strong collaboration is created between the two MHC institutions and the university in this project, with shared goals and input. Additionally, the process evaluation will be helpful in following the implementation process.

Another challenge of this study, and of most other studies among outpatients with SMI and follow-up measurements, is the dropout risk in the cluster RCT. In the sample size calculation, we take this into account by estimating a 15% loss to follow-up, and using effect sizes that may be considered conservative, compared to effect sizes found in other studies [64]. This leads to 347 required respondents at baseline measurement. Moreover, with the help of the MHPs, a contact plan, and by giving clients incentives for participating, we aim to prevent dropout as much as possible.

Finally, due to novelty of the Victoria intervention, there is no valid fidelity measure. Therefore, in this project a new fidelity checklist will be developed and used. To increase validity in measuring fidelity, we use triangulation by also including qualitative analyses of the recordings of the supervision meetings and questionnaires for both clients and MHP, as explained in the methods section.

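### The 151 per condition matches a difference averaged over two follow-ups, but the analysis section reads most naturally as comparisons at 9 and at 18 months, where power would be about 58–60% before clustering

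*Protocol article*

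**What the plan says.** All references are to the protocol article.

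- **Sample size.** A repeated-measures formula is used with four stated inputs: "the ratio of the number of subjects in the compared groups being 1", "a correlation coefficient of the repeated measurements of 0.20", "a conservative difference between the groups in the mean value of social functioning of 0.25" and "a power of 1-β = 0.80" ("α = 0.05, two-tailed"). The result is that "the number of participants needed is 151 for each condition at T2 measurement". The formula contains T and σ, but neither is given a value.
- **Statistical analyses.** One mixed model per outcome is planned. For the main outcomes "both conditions will be compared after 9 and 18 months follow-up with time as a categorical variable". A two-tailed 0.05 threshold applies to every analysis. No effect averaged over the follow-ups is named, and neither visit is singled out as primary.
- **Discussion.** Sufficient power is listed as a major strength, and the sample size is described as "using effect sizes that may be considered conservative, compared to effect sizes found in other studies".

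**The concern.** A formula with T repeated measurements gives the sample size for a difference in each client's mean over those T measurements. Averaging reduces the variance, and with a correlation as low as 0.20 it reduces it a good deal. The saving exists only if the test is made on the average. A model with categorical time yields one arm difference per visit, and a test of either one does not benefit from the averaging.

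If the effect on social functioning is judged visit by visit, the stated 80% does not apply to the result that will be read. Tying the 151 to the T2 measurement adds to the difficulty, because a reader may take it to mean 80% power at 18 months. This is separate from any loss due to clustering by team.

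**Working it through.** **Inputs stated in Sample size:** two-sided α = 0.05 (z = 1.960), power 0.80 (z = 0.842), r = 1, ρ = 0.20, v = 0.25.

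**Inputs assumed:** σ = 1, so that v is a standardised difference. The Discussion supports this by speaking of effect sizes. T is inferred from the result below. The 2 printed after the sum of the z terms is read as a square.

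**Step 1: reproduce the 151.**

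N = (z₁₋α/₂ + z₁₋β)² σ² (r + 1)[1 + (T − 1)ρ] / (v² r T), with (1.960 + 0.842)² = 7.849 and v² = 0.0625.

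| T | Calculation | N per condition |
|---|---|---|
| 1 | 7.849 × 2 × 1.0 / (0.0625 × 1) | 251.2 |
| 2 | 7.849 × 2 × 1.2 / (0.0625 × 2) | 150.7, rounded up to 151 |
| 3 | 7.849 × 2 × 1.4 / (0.0625 × 3) | 117.2 |

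Only T = 2 gives the stated figure, and the design has two follow-ups. T = 1 is also hard to square with the inputs, because ρ would then drop out of the formula although the protocol lists it.

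**Step 2: what T = 2 powers.** The variance factor is (1 + 0.20)/2 = 0.6, the variance of the mean of two measurements correlated at 0.20. The 151 therefore belongs to the averaged difference.

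**Step 3: power of the possible contrasts with 151 per condition.** For a contrast with variance factor k, power = Φ(0.25/√(2k/151) − 1.960).

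| Contrast | k | 0.25/SE | Power |
|---|---|---|---|
| Average of 9 and 18 months | 0.6 | 2.804 | 80.1% |
| One visit, unadjusted | 1 | 2.172 | 58.4% |
| One visit, baseline-adjusted | 1 − 0.20² = 0.96 | 2.217 | 60.1% |
| One visit, change from baseline | 2(1 − 0.20) = 1.6 | 1.717 | 40.4% |

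For a joint two-degree-of-freedom test of both visits, the non-centrality is 2 × 2.172² / 1.2 = 7.86 (from the unrounded ratio), which gives 71.0%.

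Counting the trial as positive if either visit reaches p < 0.05 gives 79.6% by simulation, but the type I error is then 9.6%. Requiring both visits gives 37.2%.

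**Step 4: size needed for one visit.** From Step 1 with T = 1, 251.2 rounds up to 252 per condition at that visit. That is 252/151 = 1.67 times the stated number.

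All these figures assume a constant 0.25 effect at both visits, correlation 0.20 throughout and no team effect.

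**The case against.** **The text does not say the visits are tested separately.** This stands. There is one mixed model, and no per-visit p-value is written. A reader might infer that the protocol commits to two separate tests and is therefore a 58%-power trial. The document does not go that far. The sentence could also cover a condition effect across both follow-ups with time as a categorical covariate, for which 151 gives the stated 80%, or a joint test, for which it gives about 71%. The per-visit comparison is the natural reading, not the only one.

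**T and σ are inferred.** This also stands. With a different σ, another T could return 151. The choice σ = 1 and T = 2 is well supported, by the effect-size wording, by the two follow-ups and by 150.7 rounding up to 151. It remains an assumption.

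**The 58% is one point in a range.** True. The article does not say how baseline enters the contrast, and the per-visit figures run from about 40% to about 60%.

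**The detail may sit in an analysis plan or full protocol that is not shown.** A missing hierarchy of contrasts would not be a finding for that reason. But the article does state a comparison for the main outcomes, and on its natural reading that comparison differs from the one behind the article's own sample size.

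A reader might also infer that 151 is a miscalculation. It is not: the figure reproduces. The issue is which contrast it belongs to.

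**Conclusion.** The point holds as a mismatch between two sections that should be reconciled. Assuming σ = 1 and T = 2, the 151 per condition gives 80% power for the arm difference averaged over 9 and 18 months. The analysis section names no such average. If the arms are compared at each visit, a true difference of 0.25 SD at a given visit would be missed about four times in ten, before any loss from clustering. None of the per-visit contrasts, nor the joint test, reaches 80% with the type I error held at 5%.

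Confidence in the arithmetic is high. Confidence that per-visit testing was intended is moderate. Because the gap before clustering closes if the average was meant all along, this should be fixed but is not in itself a failure of the design.

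**What to change.** Make the Sample size and Statistical analyses sections refer to the same contrast, and state T and σ beside the formula. There are two ways to do it.

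1. **Average as primary.** State that the primary contrast for social functioning is the equally weighted average of the 9- and 18-month arm differences, estimated from the same mixed model, with each visit reported separately as secondary. This keeps the 151 and the 80% before clustering. It takes one sentence and changes neither recruitment nor data collection. The downside is that an effect present only at 18 months is diluted.
2. **18 months as primary.** Say so, and restate the power with 151 per condition as about 58% unadjusted or about 60% with baseline adjustment, before clustering. Amend the Discussion's statement on sufficient power to match. Keeping 80% for this contrast would instead need 252 per condition at that visit for the unadjusted comparison.

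Neither option deals with clustering by team, which would lower all these figures if clients within a team are correlated.
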